### Recruitment {15}

Random selection of schools to be invited to participate in the trial was based on the official list provided by the Ministry of Education (FWB). In order to ensure a good coverage of the school population, it was stratified by region (Brussels/Wallonia) and by the school socio-economic index (SSEI) stratum (*n* = 3). The SSEI is scored following several characteristics of the families attending the school [48]. We used the tertiles of the SSEI to identify the low, intermediate, and high SSEI of primary schools.

Once they were selected, we contacted the schools to inform them of their selection and to describe the research. Reasons for school refusals were collected (as well as for possible further withdrawal). Among 1379 eligible schools, 168 have been sampled (baseline participation rate: 29%). When they accepted to be part of the research, the first data collection was planned. Ultimately, the six strata of schools are suitably balanced among the participating schools. Furthermore, all school networks are represented.

As a cluster trial, all pupils of the schools in intervention groups receive the intervention. Furthermore, in accordance with the ethical committee advice (see below), no specific recruitment process has been developed for the pupils, except through the letters of information about the data collection.

## Assignment of interventions: allocation

### Sequence generation {16a}

After the first wave of data collection, we assigned the schools to the four groups. All schools were randomly numbered (“rununiform” command in Stata®), and allocation was made by dividing the schools into 4 equal groups. The allocation process was blinded to any information related to schools in an independent database.

### Concealment mechanism {16b}

Given the kind of intervention planned in the DRINK project, further steps cannot be blinded since informing schools and the research team is necessary to achieve the project.

### Implementation {16c}

As soon as the randomisation was made, schools, including those from the control group, were informed of their attributed group.

## Assignment of interventions: blinding

### Who will be blinded {17a}

As an open-label study, it is not possible to blind schools, parents, and children. However, the allocation group is not mentioned in the questionnaires and in the 4-day booklets. During the intervention period, it is also essential for the research team to know the allocation group (for the preparation of information documents, for example). Once the first objective analyses are undertaken, data analysts will be blinded to the allocation group (also see the “Statistical methods for primary and secondary outcomes {20a}” section).

### Procedure for unblinding if needed {17b}

The design is open label with only outcome assessors being blinded so unblinding will not occur.

## Data collection and management

### Plans for assessment and collection of outcomes {18a}

At each wave of evaluation (Fig. 3), we collect information from the school staff, children, and parents. The school staff answer a face-to-face 1-h questionnaire with a dietitian about health promotion actions related to nutrition and sustainability fields including dietary recommendations and food supply, access to tap water, environment-related activities, parents’ involvement in the school activities, and impact of COVID-19 pandemic. In the intervention groups, their perception of the intervention content and organisation is also documented (2nd wave). Repeating such an information collection and completing it with specific questions on their perception about the research at 2nd and 3rd waves will enable to measure the school adherence to the interventions in addition to the participation rates at each evaluation.

Children’s and parents’ self-completed paper questionnaires focus on living conditions, dietary habits, and sustainability components (Table 2). Children complete the questionnaire at school while parents fill it in at home. Some questions come from the HBSC surveys carried out in French-speaking Belgium; therefore, these have been validated elsewhere; others come from validated tools (Table 2). Questions are divided between the two questionnaires depending on the capacity of children to answer them (e.g. parents’ occupation asked in the parents’ questionnaire). A pre-test was undertaken in several classes of a voluntary school (not included in the trial) to improve the wording and simplify some questions, which were too difficult for children of this age.

**Table 2 Tab2:** Topics^a^ addressed in the questionnaires self-completed by children and parents

	**Children**^**b**^	**Parents**^**c**^
Drink consumption behaviour	Beverage frequency questions (*n* = 6) *Sugar liking* [49] Thirst perception^d^ *Peer influence* [50, 51] Marketing influence [52] Beverage accessibility at home^d^ Tap/bottled water use at home and school^d^	Drinks given for lunchbox, snacks and origin (manufactured, homemade) Home rules for accessibility *Reasons for choosing beverages*
Food consumption behaviour	Short food frequency questionnaire (*n* = 12) Weekly breakfast frequency	Fast-food frequency
Environmental risk perception and behaviour	Behaviour to decrease environmental impact [53, 54]	*Perception of environmental risks* [55] Sensitivity to packaging waste
Health status and behaviour	Self-perceived health status Body weight perception *Tooth brushing*	Declared weight and height^e^ *Sleeping time* *Last dentist visit, previous decay* *Transportation, sport, outside playtime*, *screen duration* Parental perception of physical activity
Demographics: socioeconomic status and conditions of living	School grade, sex, month/year of birth^d^	School grade, sex, month/year of birth
	Family affluence scale	*Parents’ occupation, school attainment*
	*Country of birth*^d^ *Acculturation scale* [56]	*Parents’ country of birth*
	*Siblings*, household composition^d^	
Well-being and social relationship	Satisfaction of life Well-being at school (overall, work, *teachers*) *Friendship* *Perceived self-efficacy* *Relationships with parents*	*Parental role modelling* [57] *Expectation for child’s future* Relationship and* involvement at school* Perception of the school’s role in children’s health^f^

^a^Data in italics are topics addressed only at the 1st wave of data collection

^b^In children, questions come from the HBSC surveys [58] unless another reference is mentioned

^c^In parents, most questions were developed or adapted for the DRINK project unless a reference is mentioned

^d^Children’s questions developed for the DRINK project

^e^Parents are encouraged to measure children

^f^Question asked at wave 2 only

A booklet has been developed and tested for collecting information on beverage consumption. This is a 4-day diary where children use stickers to describe the moment of the day (10 different stickers), type (13), and amount of each beverage consumed (22). They are also encouraged to write information about the characteristics of the beverage (brand and taste) and any additions such as sugar, syrup, or cacao. In 2021, a calibration study was conducted on 114 children to compare declarations, on the same given day, through a 24-h recall administrated by a paediatric dietitian on the phone (considered as the method of reference) and information collected in the booklet. A calibration error will be computed and used at the time of analysis [59].

### Plans to promote participant retention and complete follow-up {18b}

School decision-makers were consulted when the protocol was developed; we collected their opinion mainly about the objectives, the interventions, and the methods to include and follow the schools up. Therefore, research is calibrated to be acceptable for a rather long duration by the school staff, who are frequently requested for various issues, including other studies. Regular email and phone contacts are carried out to enhance the involvement of schools in the project, along with a newsletter describing the progress of the research itself. It is also sent to control group #4 with information on data collection only and without mention of the intervention. The second and third audits at schools include questions about their perception of the research burden, including intervention and organisation for data collection.

### Data management {19}

Daily monitoring is ensured by using tools shared in the research team that help follow up contacts with schools (participation, data collection and intervention material; organisational issues) and to monitor the inclusion and participation at any stage of the project (participating schools and number of questionnaires/4-day booklets received and completed). The school staff manage the list of correspondence between the ID number and names and save an encrypted copy of the list in the server of the School of Public Health (ESP-ULB). Such a list is necessary for the follow-up of each child over time.

When they are sent back to ESP-ULB, parents’ and children’s paper questionnaires are checked for the corresponding ID numbers and for the readability of the written information. They are then sent for a numerical scanning to a specialised firm. A codebook we provided is used by the firm to develop the database containing only numerical codes. Databases are checked for by comparing them with the monitoring tools (ID numbers) and with the codebook (codes’ ranges). Some key frequencies are verified to detect other potential mistakes at the time of scanning. After this first step, outlying values for continuous variables and consistency between some key questions are evaluated. Initially filled in on paper by the dietitians, schools’ audit questionnaires are entered into a form developed using the Limesurvey® software. They include categorical questions which are coded, and free-space texts, which are also entered to facilitate their subsequent analysis.

Lastly, 4-day booklets are entered using an Excel® form specifically developed for the project. A first quality control is made at the time of entry by signalling booklets which will need to be checked one by one for their plausibility and their completion. After the development of the database, the Stata® software is used to recode the inconsistencies (for instance, cacao added to a soup) and to identify extreme amounts of beverage consumption (for each intake and total for each day). All databases are safely stored on the cloud managed by ULB.

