### Outcomes {12}

The first quantitative judgement criterion will be the change over time in the mean SB consumption (in ml/day) in the intervention groups compared with the control group (Fig. 1). The secondary criteria of judgement will be the change in the proportion of children consuming SB each day on the one hand and in the mean consumption of water (in ml/day) on the other hand. Quantitative outcomes in ml/day will be evaluated through a 4-day booklet, while the daily consumption will be based on a short frequency questionnaire. These outcomes will be measured at the second wave of data collection and changes estimated by difference with the pre-intervention measurements. Findings at the first post-intervention data collection will also be presented once the trial is finished.

Among the secondary objectives of the DRINK trial, the same outcomes will be used to assess the potential interaction between nutrition- and sustainability-based interventions (Fig. 1). The other three secondary objectives will be assessed using complementary information as described below. Altogether, the information collected and the regular monitoring of the trial development (including cost which is one of the objectives) will also enable to develop a comprehensive process evaluation.

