## Statistical methods

### Statistical methods for primary and secondary outcomes {20a}

After presenting the characteristics of each group at baseline, statistical analysis will include assessment of the primary and secondary criteria of judgement and secondary objective. Intention-to-treat analyses will be carried out. At the time of statistical analyses, the group allocation will be blinded in the database.

For the effectiveness criteria of judgement, multilevel regression analyses will be used to consider the randomisation by cluster (and not by individual) since the number of clusters is rather high (48 schools) [60]. Differences in the beverage consumption (in ml/day, from the 4-day diary) between the endpoint and the initial assessment (undertaken before trial allocation of schools) will be computed for each child followed up over this period, such values being the outcome to evaluate. We will also compare the proportions of children drinking SB each day based on the frequency questions. After analysing the 2-year post-intervention vs. initial data, we will carry out the same analyses at 1-year post-intervention among (1) all children followed up for 2 years and (2) children with data available at inclusion and at 1-year post-intervention. This complementary assessment will contribute to the understanding of the trial effectiveness, if any.

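### The only masking given a time starts at statistical analysis, after flagged primary-outcome booklets have been judged for plausibility, and the protocol does not say whether the people who judge them know the school's group.

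*Protocol article*

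**What the plan says.** All references are to the protocol article.

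- **Source of the outcome.** Outcomes {12}: "Quantitative outcomes in ml/day will be evaluated through a 4-day booklet". Under {20a} the analysed value is each child's endpoint amount minus the initial amount.
- **Cleaning.** Data management {19} has a first quality control at entry, "signalling booklets which will need to be checked one by one for their plausibility and their completion". After the database is built, "the Stata® software is used to recode the inconsistencies (for instance, cacao added to a soup) and to identify extreme amounts of beverage consumption", both per intake and per day. The section does not say who does any of this.
- **Allocation.** Sequence generation {16a} puts allocation after the first wave of data collection. Concealment {16b} says that what follows allocation cannot be blinded, because schools and the research team have to be informed.
- **Team knowledge.** {17a}: "During the intervention period, it is also essential for the research team to know the allocation group". The same section says that the booklets do not show the group.
- **Masking.** {17a} blinds the data analysts when the first-objective analyses are undertaken. {20a}: "At the time of statistical analyses, the group allocation will be blinded in the database". {17b} describes an open-label design in which only outcome assessors are blinded, without defining them.
- **Dates.** The Abstract places the interventions from February 2022 to June 2023. Trial status has wave 2 finishing at the beginning of 2023 and wave 3 planned for April to December 2023.

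**The concern.** Whether a child's diary is plausible or complete is a judgement, and the ml/day value is final only once that judgement has been made. If the person making it knows that a school is a control or an active school, decisions on borderline booklets can lean one way. Concealing the group from the analyst afterwards does not help, because the data already carry those decisions.

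The design makes this a matter of follow-up data in particular. Wave 1 booklets were collected before allocation and later booklets after it, so the two halves of a change score may have been cleaned under different knowledge of the group. The protocol states when masking begins, and that moment comes after the step where masking would matter most for the primary outcome.

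**Working it through.** **1. Order of events**

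| Step | Section | Masking stated? |
|---|---|---|
| Booklets gathered by teachers and sent to the research team | {27} | Group not printed on the booklet ({17a}) |
| Entry, flagging, one-by-one check of flagged booklets | {19} | None |
| Recoding of inconsistencies, identification of extremes | {19} | None |
| Statistical analysis | {17a}, {20a} | Allocation masked in the database, analysts blinded |

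Four statements then have to be read together: {16b} (no blinding after allocation), {17a} (team knows the groups, analysts masked at analysis), {17b} (outcome assessors blinded) and {20a} (database masked at analysis). If the assessors in {17b} include the booklet checkers, {16b} and {17a} need an exception for them. If the assessors are the analysts, masking comes after cleaning. The text does not settle which.

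**2. Could the checkers know the group?** No passage says so. Three passages make it possible:
- {27}: booklets reach the research team from the schools.
- {19}: the team's shared tools cover both intervention material and the receipt of booklets. An outside firm is named for scanning the questionnaires but none for the booklets.
- {5d}: the coordinating centre's meetings deal with both intervention steps and data quality.

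**3. The plan's own scale, from Sample size {14}.** Inputs: mean 200 ml/day, SD 120, a 15% reduction (30 ml/day), alpha 5% (taken as two-sided), power 80%, ICC 0.08, and 4 × 17 = 68 pupils per school.
- n per side without clustering = 2 × (1.960 + 0.842)² × 120² / 30² = 251.2, so 252.
- Design effect = 1 + (68 − 1) × 0.08 = 6.36.
- 252 × 6.36 = 1,603 per side, or about 3,205 in total. 1,603 / 68 = 23.6, so 24 schools per side and 48 in all. The plan's 48 schools and roughly 3,200 pupils are reproduced and are not in dispute.
- Effective n per side = 24 × 68 / 6.36 = 256.6. Standard error of a factorial margin = 120 × √(2 / 256.6) = 10.6 ml/day.

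**4. Illustrative shift.** The documents give no input for this. Assume that a share q more of the diaries lying X ml/day above the mean are dropped, or recoded to about the mean, in one group than in another. The contrast moves by about q × X.
- q = 0.02, X = 300: 6 ml/day (6 / 30 = 20% of the planned effect).
- q = 0.02, X = 500: 10 ml/day (33%).
- q = 0.01: 3 to 5 ml/day.

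**5. In the planned factorial comparison.** {6b} compares groups 1 and 3 with groups 2 and 4, so active schools stand on both sides. If handling shifts every active group by b and the control group by 0, the margin moves by (b + b)/2 − (b + 0)/2 = b/2. The 6 to 10 ml/day becomes 3 to 5 ml/day, or 10% to 17% of 30 ml/day.

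**6. Effect on the error rate.** With a standard error of 10.6 and no true effect, the two-sided type I error of a margin is 5.9% at a shift of 3 ml/day, 7.6% at 5 and 15.7% at 10, instead of 5%. A 10 ml/day shift in a margin needs handling that differs along that factor itself, not merely between control and active schools.

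**The case against.** A reader might infer that the booklets are checked and recoded by people who know each school's group. The protocol does not say that. The cleaners are not identified, the booklets carry no group label, {17b} says that outcome assessors are blinded, and {17a} ties the team's knowledge to work such as preparing information documents. That objection stands: unmasked cleaning is a possibility left open, not a documented fact.

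Several narrower objections also stand:
- Only flagged booklets are checked singly. The recoding is a later Stata step, and its example (cacao in a soup) looks like a fixed rule. Extreme amounts are identified, and nothing says that they are removed.
- The primary contrast uses the two-year endpoint ({13}, {20a}), so wave 3 is what matters. Wave 2 feeds the complementary one-year analyses. Most of the wave 3 window falls after the interventions ended in June 2023, while the {17a} sentence on the team's knowledge covers the intervention period. Staff who delivered the interventions can still remember the groups, but the documents give no cleaning dates for any wave.
- The 2-point difference is generous. Diaries 300 to 500 ml/day above the mean lie 2.5 to 4.2 SD out, and under a normal distribution no more than about 0.6% lie that far. The illustration needs a right-skewed distribution, which the documents neither show nor exclude.
- Detailed cut-offs and completeness rules are commonly kept in a data management plan or SAP, and their absence from an article is no fault.

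These points do not remove the gap in timing. The protocol does fix when masking begins, and the point it fixes comes after a judgement step on the primary outcome. {17b} cannot close the gap while the assessors are undefined, the more so because the children who record the outcome are themselves unblinded.

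**Conclusion.** The point holds in a limited form. Flagged booklets for the primary outcome go through case-by-case checks, the research team is unblinded after allocation, and the only masking given a time starts later, at analysis. The blinding statements in {16b}, {17a}, {17b} and {20a} do not make clear whether booklet checkers are masked, so group-dependent cleaning at follow-up is not ruled out.

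The size cannot be established from the documents. The range of 6 to 10 ml/day for a two-group contrast, or 3 to 5 ml/day in a factorial margin when only control and active schools are treated differently, rests on an assumed 2-point difference in handling and assumed excesses of 300 to 500 ml/day. It shows only that modest differences in handling could matter against a 30 ml/day target. It is not evidence that bias has occurred, and the sample size is unaffected. The change is worth making because it is nearly free and wave 3 was still to come when the article was written.

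**What to change.** 1. In {17a}, {19} and {20a}, move the start of masking ahead of the booklet checks. Wave 3 checks, and any re-check of wave 2, should be done on records re-keyed to a random number, without school code or group, and in mixed school order.
2. Apply the same scripted recoding and extreme-value rules to all waves, fixed without reference to group. Wave 1 booklets, collected before allocation, are a natural basis. The details can sit in the data management plan or SAP, with {19} stating the principle.
3. Reconcile {16b}, {17a}, {17b} and {20a}: say who the outcome assessors are, whether they include those who enter and check booklets, and from what moment each role is blinded.
4. Report the numbers of booklets flagged, excluded and recoded by group and wave.

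The cost is a few days of programming for the rule set and the re-keyed export, and possibly a re-run of wave 2 cleaning. No additional staff or data are needed.

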### Confidentiality {27}

As described above, the research team has no access to any nominative information. Like any other health workers, researchers are committed to respect confidentiality rules. Children’s and parents’ documents are provided in numbered envelopes that they can keep throughout the data collection period, so that school staff cannot read answers to questionnaires and 4-day booklets. Furthermore, teachers are explicitly encouraged to respect the confidentiality of answers when children complete the self-administrated questionnaire in class and when they gather the 4-day booklets before sending them to the research team.

### Plans for collection, laboratory evaluation, and storage of biological specimens for genetic or molecular analysis in this trial/future use {33}

No biological specimens are collected (also see the “Additional consent provisions for collection and use of participant data and biological specimens {26b}” section).

## Statistical methods

### Statistical methods for primary and secondary outcomes {20a}

After presenting the characteristics of each group at baseline, statistical analysis will include assessment of the primary and secondary criteria of judgement and secondary objective. Intention-to-treat analyses will be carried out. At the time of statistical analyses, the group allocation will be blinded in the database.

For the effectiveness criteria of judgement, multilevel regression analyses will be used to consider the randomisation by cluster (and not by individual) since the number of clusters is rather high (48 schools) [60]. Differences in the beverage consumption (in ml/day, from the 4-day diary) between the endpoint and the initial assessment (undertaken before trial allocation of schools) will be computed for each child followed up over this period, such values being the outcome to evaluate. We will also compare the proportions of children drinking SB each day based on the frequency questions. After analysing the 2-year post-intervention vs. initial data, we will carry out the same analyses at 1-year post-intervention among (1) all children followed up for 2 years and (2) children with data available at inclusion and at 1-year post-intervention. This complementary assessment will contribute to the understanding of the trial effectiveness, if any.

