### Sample size {14}

The sample size determination is based on the cluster-randomised factorial plan [45, 46]. The following assumptions have been set for the first criterion of judgement: (i) observed mean of SB consumption, i.e. 200 ml/day (SD: 120 ml) [47]; (ii) a 15% reduction in the intervention group (either nutrition or sustainability), i.e. mean 170 ml/day at the last 2-year follow-up and stability in the control group; (iii) type I error (alpha) of 5%; (iv) statistical power of 80%; and (v) intra-class correlation of 0.08 (estimation based on the “Health Behaviour in School-aged Children” (HBSC) survey carried out in 2018 in French-speaking Belgian primary schools) [48]. The theoretical total number of schools needed is estimated at 48, corresponding to around 3200 students surveyed during the 2 years (based on the same 2018 HBSC survey: on average, four classes in each participating school and 17 students in each of these classes). Since we use a factorial plan, 12 schools are allocated in each group (Fig. 1).

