### Methods for additional analyses (e.g. subgroup analyses) {20b}

Regressions will be adjusted for various characteristics related to beverage consumption in children and parents, and differences between schools at randomisation. Adjustment variables will be chosen based on the differences observed between the randomised groups at inclusion. Stratified analyses are planned based on the inclusion characteristics already chosen: child body weight status, family socio-economic status, and some school indicators such as SSEI and province. Purposely, a predefined and limited number of stratified analyses will be undertaken, and repetition of analysis will be corrected for.

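### The primary analysis uses each child's raw change in SB intake without committing to baseline adjustment, and the 80% power was calculated for an endpoint comparison rather than for that change

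*Protocol article*

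**What the plan says.** Outcomes {12} defines the primary criterion: "The first quantitative judgement criterion will be the change over time in the mean SB consumption (in ml/day"), intervention against control. Statistical methods {20a} turns this into a child-level variable: "Differences in the beverage consumption (in ml/day, from the 4-day diary) between the endpoint and the initial assessment" (the latter made before allocation) "will be computed for each child followed up over this period, such values being the outcome to evaluate", and "multilevel regression analyses will be used to consider the randomisation by cluster". The child's baseline intake is not named as a covariate there.

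Covariates appear under additional analyses, {20b}: "Regressions will be adjusted for various characteristics related to beverage consumption in children and parents, and differences between schools at randomisation". The next sentence gives the selection rule: "Adjustment variables will be chosen based on the differences observed between the randomised groups at inclusion".

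Sample size {14} rests on "observed mean of SB consumption, i.e. 200 ml/day (SD: 120 ml") and on "a 15% reduction in the intervention group (either nutrition or sustainability), i.e. mean 170 ml/day at the last 2-year follow-up", with stability in the control group, an intra-class correlation of 0.08, and four classes of 17 pupils per school. It gives no SD of the change and no correlation between baseline and endpoint.

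**The concern.** Two things do not fit together well.

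First, subtracting the baseline fixes its coefficient at 1, whatever the data say about how far baseline intake predicts intake two years later. The instrument is a 4-day sticker diary completed by children, for which the investigators themselves ran a calibration study, and the two diaries are two school years apart. A coefficient of 1 is then unlikely to be the efficient choice. The selection rule in {20b} does not repair this: it lets baseline intake in only if the groups happen to differ, and it leaves the model undetermined until the baseline data have been compared.

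Second, the trial was sized on the spread of a single measurement but will be analysed on the spread of a difference. The two are equal only at one particular correlation. Precision on the primary outcome is at stake, and so is whether the 80% power describes the analysis that will be run.

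**Working it through.** **Inputs from Sample size {14}:** difference 200 − 170 = 30 ml/day; SD 120; alpha 5% (two-sided reproduces the stated size, one-sided does not); power 80%; ICC 0.08; 4 × 17 = 68 pupils per school; 12 schools per group, hence 24 against 24 for each factorial main effect. **Assumed:** baseline-endpoint correlations, and equal variances at both waves.

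**1. The plan's own figure.** Two means with SD 120 and difference 30 need 252 pupils per arm. The design effect is 1 + 67 × 0.08 = 6.36. Then 252 × 6.36 = 1603 per arm, 3205 in total, and 3205/68 = 47.1 schools, rounded up to 24 per side, or 48. This matches the stated 48 schools and about 3200 pupils. Power with 24 against 24 schools is 80.8% (normal approximation; 79% with a t distribution on 46 df), so there is almost no slack.

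**2. Precision of change against adjustment.** With correlation r, the change has variance 2(1 − r)σ² and the baseline-adjusted outcome (1 − r²)σ². The ratio is 2/(1 + r), above 1 for every r below 1: 1.67 at r = 0.2, 1.33 at 0.5, 1.11 at 0.8. The change has the SD used for sizing only if 2(1 − r) = 1, that is r = 0.5.

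**3. Which correlation matters.** The variance of a school mean splits into

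- between schools: 0.08 × 14,400 = 1152
- within schools: 0.92 × 14,400/68 = 194.8
- total: 1346.8, of which 1152/1346.8 = 86% is between schools.

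So school-level stability over two years drives power far more than the stability of one child's diary.

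**4. Power with 48 schools, pupil-level correlation 0.3 (assumed).** With school-level correlation c, the change in a school mean has variance 2(1 − c) × 1152 + 2(1 − 0.3) × 194.8. The correlation of school means is R = (c × 1152 + 0.3 × 194.8)/1346.8, and the adjusted variance is 1346.8 × (1 − R²). The standard error of the group difference is √(2 × variance/24), and power is Φ(30/SE − 1.96).

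| c | variance of change | R | power, change | power, adjusted | variance ratio |
|---|---|---|---|---|---|
| 0.4 | 1655 | 0.39 | 72% | 87% | 1.44 |
| 0.6 | 1194 | 0.56 | 85% | 93% | 1.28 |
| 0.8 | 734 | 0.73 | 97% | 98% | 1.16 |

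Across school-level correlations of 0.4 to 0.8 and pupil-level correlations of 0.3 to 0.7, change-score power runs from 72% to 99% and the variance ratio from 1.44 down to 1.12.

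**5. Sensitivity to chance imbalance.** The standard error of the baseline difference between 24 and 24 schools is √(2 × 1346.8/24) = 10.6 ml/day, about 35% of the 30 ml/day target. A change score subtracts an imbalance in full; an adjusted analysis subtracts R times it. For an imbalance of one standard error the two estimates differ by (1 − R) × 10.6: 6.5, 4.7 and 2.9 ml/day in the three rows above.

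**The case against.** The strongest defence is that nothing here is invalid. Schools were randomised after the first wave, so the change score is unbiased, keeps its type I error, and matches the outcome as defined in {12}. A reader might infer that regression to the mean biases the result. It does not: it is equal across groups in expectation and matters only when baseline intake is imbalanced by chance. In that case {20b} may bring baseline into the model, and a change-score model with baseline as a covariate gives the same treatment estimate as ANCOVA. All of this stands.

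A reader might also infer that the trial is underpowered, because a child's diary correlates only moderately with itself over two years. Applying r = 0.3 throughout, with the ICC kept at 0.08, gives 67% power. But keeping 0.08 for the change amounts to assuming that the school-level correlation is also 0.3. With a pupil-level correlation of 0.3 and a school-level correlation of 0.6, the overall child correlation is only 0.08 × 0.6 + 0.92 × 0.3 = 0.32, yet power is 85%. The article gives neither value, so the inference is not supported.

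Finally, a condensed article may leave the covariate list to a fuller plan. That would excuse silence, but the article is not silent: it fixes the outcome variable and states an imbalance-based selection rule. Neither that rule nor the general statement about adjustment commits to baseline intake. This part of the defence does not stand.

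**Conclusion.** The point holds as one of efficiency and of a mismatch between sizing and analysis. For any correlation below 1 the raw change is less precise than a baseline-adjusted analysis, by a factor 2/(1 + r) in variance under equal variances; that ordering does not depend on which correlation is assumed. The sample size is arithmetically correct for an endpoint comparison with SD 120, but it does not establish 80% power for the change. Whether that power falls short or exceeds 80% turns mainly on an unstated school-level correlation. In these calculations change-score power equals the endpoint figure of 80.8% when school means correlate at R = 0.5, is lower below that and higher above it.

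The power figures rest on the planning inputs (68 pupils per school, ICC 0.08, equal variances) and on assumed correlations. They show a possible shortfall, not a demonstrated one. Severity: should be fixed.

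**What to change.** In the primary multilevel model, prespecify the child's baseline SB intake and the school baseline mean as fixed covariates, whatever imbalance is observed. Endpoint or change may be the dependent variable: with the same covariates the treatment estimate is identical and still read in ml/day, so the definition in {12} can stay. Do the same for water intake, and include baseline status in the analysis of daily SB consumption.

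In Sample size {14}, either state the SD of change or the correlation behind the 80% power, or say that the power refers to an endpoint comparison.

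The cost is a few sentences in the analysis plan, settled before the analysis. No new data are needed, because baseline intake was collected before allocation.
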